### **3. PROJECT AIMS**

#### **Specific aim 1**

To develop a biomarker-based diagnostic algorithm for FMD by modeling behavioral, neurophysiological, and MRI biomarkers to investigate the motor, exteroceptive and interoceptive domains. Deep learning will be used, and visualization and interpretability methods will be exploited to identify the most sensitive measures. The results obtained will determine which biomarkers are the hallmarks for FMD diagnosis identifying the key differences between FMD and healthy controls.

#### **Specific aim 2**

To test the validity of the resulting biomarker-based diagnostic algorithm against patients with "organic" motor disorders to evaluate its specificity for FMD. The results obtained will determine which biomarkers are specific for FMD diagnosis identifying the key differences between FMD and patients with "organic" motor disorders.

#### **Specific aim 3**

To explore whether the validated biomarkers change after a multidisciplinary rehabilitation training and correlate them with changes in quality of life and motor and non-motor symptoms of FMD patients to determine their potential role in measuring treatment response and giving prognostic information.

We hypothesize that a composite panel of clinical, neurophysiological, and neuroimaging biomarkers covering motor, exteroceptive and interoceptive domains would be instructive in the diagnosis and prognosis of FMD from the earliest symptoms onset. It would allow the correct diagnosis of these patients early and delineate specific management pathways for future intervention trials with positive socio-economic impact.

### **4. SUBJECTS**

#### **Experimental design 1.**

150 patients with a clinically definite diagnosis of FMD based on Gupta and Lang diagnostic criteria (1) and 150 matched HC consecutively recruited by Unit 1 (75 patients and 75 HC) and Unit 2 (75 patients and 75 HC) (WP1).

Inclusion criteria for patients will be age higher or equal to 18 years and a clinically definite diagnosis of FMD (1). Exclusion criteria for patients will be Mini-Mental State Examination score lower or equal to 24; physical impairment precluding signing the informed consent for participation; certified neurological and/or psychiatric comorbidities (i.e., neuropathy, seizures, major depression); contraindications for 3T MRI.

Inclusion criteria for HC will be age higher or equal to 18 years; Exclusion criteria for HC will be Mini-Mental State Examination score lower or equal to 24; physical impairment precluding signing the informed consent for participation; certified neurological and/or psychiatric comorbidities (i.e., neuropathy, seizures, major depression); contraindications for 3T MRI.

### **Experimental design 2.**

150 additional patients with "organic" motor disorders (50 patients with weakness due to peripheral neuromuscular disorders; 50 with ET according to the 2018 consensus criteria (2); 50 with idiopathic adult-onset dystonia) recruited by Unit 1 (75 patients) and 2 (75 patients) (WP4). ET patients will undergo a neurological assessment by a movement disorder specialist. Patients with idiopathic adult-onset cervical or limb dystonia, either focal or as part of a segmental/multifocal dystonia, will be diagnosed according to published criteria (3). Patients with muscle diseases including idiopathic inflammatory myopathies, sporadic inclusion body myositis and limb-girdle muscular dystrophies will be evaluated according to published criteria (4).

We will assess the same biomarkers identified in the diagnostic biomarker algorithm (experiment 1) in 150 patients with organic motor disorders recruited from Unit 1 and Unit 2 (2-4).

Additional exclusion criteria will be score >2 on the Tremor Research Group Essential Tremor Rating Assessment Scale; rest tremor and other neurological signs; current or past exposure to tremorigenic drugs. Demographic and clinical findings will be collected. Tremors and dystonia severity will be rated using the Fahn-Tolosa-Marin TRS and the Burke-Fahn-Marsden scale. Anxiety, depression, alexithymia, and QoL will be evaluated through the BAI, BDI II, and SF-12.

### **Experimental design 3.**

34 out of 75 patients with a definite diagnosis of FMD (aim 1, Unit 1) will be drawn and tested by the same biomarkers identified in the diagnostic biomarker algorithm (experiment 1) in FMD before (T0) and after 3 months (T1) of a validated 5-day rehabilitation protocol (2 h/day) within a multidisciplinary etiological framework followed by telemedicine program (8,23-25). Patients will be randomly selected from the cohort of patients with FMD recruited in experimental 1 at Unit 1 (n=75), picking a random number from a computer-based list of 75 items. The same inclusion/exclusion criteria of experiment 1 will be used for patients' enrollment. The validated 5-day rehabilitation treatment will be performed by the one physiotherapist participating in the research project. The same physiotherapist will perform the telemedicine program. The rehabilitation treatment will be performed in the rooms of the USD Malattia di Parkinson e Disordini del Movimento, AOUI Verona, under the supervision of the Co-PI (Prof.ssa [name]). At T0 and T1, we will perform the same clinical scales and biomarkers included in the biomarker-based diagnostic algorithm (experiment 1) The fMRI task will consist of self-paced alternate dorsal/plantar foot flexion movements (5) with and without cognitive and visual dual-task (6,8).

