#### **Experimental design aim 3**

A prospective longitudinal study on 34 out of 75 patients with a definite diagnosis of FMD (aim 1) randomly recruited by Unit 1 will be performed. The diagnostic biomarker algorithm resulting from experiment 1 will be tested in patients with FMD before (T0) and after 3 months (T1) of a rehabilitation protocol validated at Unit 1 (WP5) (13). A physician expert in movement disorders will assess patients at each time point through validated clinical scales to assess motor and non-motor symptoms, depression, anxiety, alexithymia, and QoL

as reported in the Methodologies section. A task-based fMRI paradigm to evaluate functional brain reorganization of sensorimotor and non-motor networks induced by rehabilitation and correlations with clinical improvement will be implemented and performed before rehabilitation (T0) and at 3-month follow-up (T1) (5,6). fMRI data will be analyzed by Unit 3. The diagnostic biomarker algorithm through XAI methods will be tested by Unit 2 before and after rehabilitation.

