## 10. STUDY DURATION

Total duration of the study: 24 months (including data analysis)

This project includes three consecutive phases, for 6 work packages (WP) integrated to deliver our stated objectives over the project's lifetime. During the first 9 months of the project, Unit 1 and Unit 2 will recruit patients and HC, collect clinical and demographic data according to the project protocols, collect and develop behavioral, neurophysiological, and MRI biomarkers. MRI scans will be obtained from the Unit 1 and 2 and sent to Unit 3 for analysis (WP1, WP2). From 10 to 12 months, the behavioral, neurophysiological, and MRI biomarkers will be combined and processed separately by means of a data mining approach (XAI analysis) to develop a computational paradigm aiming at better defining their diagnostic value and then to validate them for Unit 1 and 2 (WP3). From 13 to 22 months, Unit 1 and 2 will assess the resulting biomarkers identified in the diagnostic biomarker algorithm (experiment 1) in FMD in a cohort of patients with "organic" motor disorders (weakness due to peripheral neuromuscular disorders, essential tremor, and idiopathic adult-onset dystonia); and the Unit 1 will evaluate the possible modulation of the diagnostic biomarker algorithm (experiment 1) before and after rehabilitation and clinical improvement of functional motor and NMSs symptoms. Unit 3 will provide MRI biomarkers for patients with "organic" motor disorders (WP4) and analyze task-based fMRI before and after rehabilitation (WP5). From 23 to 24 months, we will analyze, disseminate, and communicate the final data (WP6). Dissemination and communication (WP 6) will include the project's visual identity (logo, packaging, website, and even your email templates), public website, leaflets and flyers, social media, videos, and press releases. Dissemination activities will maximize the impact of research results in the public domain, such as the scientific community, stakeholders, policymakers, through an open science framework and patient's charity. Primary and secondary results will be exploited and disseminated through scientific papers, conferences, talks, workshops.

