## 11. SAMPLE SIZE CALCULATION

Sample size calculations are based on the simulations performed by Guo et al. 2010 (26). We will use Random Forests (RF) owing to their non-parametric nature that contributes to robust performance under settings of varying class conditional biomarkers distributions. Assuming a skewed distribution of the dataset and up to 100 neurophysiological and imaging features to include in the statistical analysis,  $k=1\%$  (where  $k$  is the percentage of biomarkers among  $n$  features measured per subject) and effect size for each biomarker  $< 0.3$ , we need a sample size of 150 subjects (75 patients with FMD and 75 HC, among all Units) using RF that ensures a statistical power  $>90\%$ , with a 4-fold cross-validation process. **To address concerns regarding the**

validity of cross-validation-based estimates in relatively small samples, we will pursue an additional external validation based on an independent test set of 150 subjects (75 patients with FMDs and 75 HC, among all Units). Finally, the diagnostic biomarker algorithm (experiment 1) will be tested against a population of patients of 150 patients with "organic" motor disorders of similar sample size (50 with weakness due to muscle diseases, 50 with ET, and 50 with dystonia, among all Units). Based on our previous study, for the rehabilitative study Unit 1 will enroll 34 patients, assuming  $\alpha = 0.05$ , power 90%, and T0-T1 rehabilitation effect size of 0.605 (mean difference 5.52; Standard deviation 9.11) on the primary outcome (SFMDRS) and a drop-out rate of 10%(8).

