## 12. STATISTICAL ANALYSIS

eXplainable AI (XAI) analysis. First, ad-hoc models will be identified based on the available data, accounting for type (multi- modal), numerosity, completeness (missing data). Then, the models will be trained and validated following k-fold cross- validation and finally tested on a new (unseen) set of data to assess their generalization properties. Classical linear methods that are the most widespread in the clinical field will be used for benchmarking. Finally, we will apply XAI methods for assessing feature relevance, and consensus will be assessed under the assumption that this will provide information about the robustness of the outcomes (27-29). This will also be investigated through association studies with parameters holding clinical relevance.

Firstly, we will employ XAI analysis using the dataset from the first recruited 150 subjects (75 FMD and 75 HC). Secondly, external validation will be performed on an independent dataset of features collected on an additional sample of 150 subjects (75 FMD and 75 HC). Finally, the biomarkers identified in the diagnostic biomarker algorithm (experiment 1) will be tested against patients with organic neurological disorders recruited by Unit 1 and 2.

For the rehabilitation sub-study, descriptive statistics will include frequency tables for categorical variables and mean and standard deviation for continuous variables. The normality of data distribution will be checked with the Shapiro-Wilk test. Parametric (paired t-test) or non-parametric tests (Wilcoxon test) will be applied accordingly to compare the means for the two-time points (T0, T1). fMRI data will be analyzed using the SPM12 software. One-sample t tests will be used to evaluate significant mean brain activations during the task. Changes over time will be evaluated using a paired t test. All the longitudinal data deriving from the rehabilitation sub-study will be handled with a complex approach named Gaussian Process Panel Modeling (GPPM). GPPM provides great flexibility because of the large number of models it can represent. It allows classical statistical inference as well as machine learning inspired predictive modeling, with the advantage of obtaining person-specific predictions of treatment response (30).

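### Some rehabilitation patients will probably be scored by an algorithm trained on them, and the protocol is inconsistent on whether T0 is the training measurement

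*Protocol*

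**What the plan says.** **Who enters the rehabilitation sub-study.** Section 4, Experimental design 3: "Patients will be randomly selected from the cohort of patients with FMD recruited in experimental 1 at Unit 1 (n=75". Thirty-four are drawn.

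**Who trains the algorithm.** Section 12: "Firstly, we will employ XAI analysis using the dataset from the first recruited 150 subjects (75 FMD and 75 HC". The rest of the cohort is held out: "external validation will be performed on an independent dataset of features collected on an additional sample of 150 subjects (75 FMD and 75 HC". The split is by order of recruitment across Units, so the 75 FMD patients of Unit 1 are spread over both sets.

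**What is done with the algorithm.** Section 2, Experimental design aim 3: "The diagnostic biomarker algorithm through XAI methods will be tested by Unit 2 before and after rehabilitation". Section 7 lists this before-and-after application among the end points.

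**When.** Section 10 builds the algorithm first: "From 10 to 12 months, the behavioral, neurophysiological, and MRI biomarkers will be combined and processed separately by means of a data mining approach". In months 13 to 22, "the Unit 1 will evaluate the possible modulation of the diagnostic biomarker algorithm (experiment 1) before and after rehabilitation".

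**What T0 is.** Section 4, Experimental design 3: "At T0 and T1, we will perform the same clinical scales and biomarkers included in the biomarker-based diagnostic algorithm (experiment 1". The Section 7 flowchart has a single biomarker collection before rehabilitation, at Visit 1 (T0). The row that marks it is also the experiment 1 collection in FMD patients and healthy controls. The only biomarker row flagged for the sub-group of 34 is the one after rehabilitation.

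**Primary outcome of the sub-study.** Section 11 sizes it on SFMDRS.

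**The concern.** A flexible classifier such as a random forest fits its own training cases closely. It gives an FMD patient in the training set a high FMD score on the stored training measurement, and a lower one on a new measurement of the same person, even if nothing has changed. If the stored measurement serves as T0, training patients have an in-sample score at T0 and an out-of-sample score at T1. The difference then contains an artefact that looks like modulation by rehabilitation.

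Aim 1 guards against this with an independent test set. Aim 3 has no such rule: the draw does not exclude training patients, and the text does not say which model scores whom. At stake is the algorithm-based part of aim 3, not the clinical comparison.

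**Working it through.** **1. The plan's own figure.** Section 11 gives effect size 0.605 (5.52/9.11 = 0.606), alpha 0.05, power 90% and drop-out 10%. Two-sided testing is assumed.

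- Normal approximation: n = ((1.960 + 1.282)/0.605)² = 28.7, so 29; 29/0.9 = 32.2, so 33.
- Noncentral t: n = 31 (power 90.3%); 31/0.9 = 34.4.

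The stated 34 is reproduced to within rounding, and this point does not alter it.

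**2. Overlap with the training set.** Let u be the number of Unit 1 patients among the first 75 FMD patients. The protocol does not fix u. The expected number of training patients among the 34 is 34 × u/75.

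| u (assumed) | Expected overlap | 95% range | Unit 1 patients held out (75 − u) |
|---|---|---|---|
| 25 | 11.3 | 7 to 15 | 50 |
| 38 | 17.2 | 13 to 21 | 37 |
| 50 | 22.7 | 19 to 27 | 25 |

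Overlap is practically certain under each split. Drawing all 34 from held-out patients needs 75 − u ≥ 34, that is u ≤ 41.

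**3. Effect on the score with no rehabilitation effect.** Taken from the protocol: random forest, 100 features, 75 FMD and 75 controls in training, and 31 completers (34 × 0.9 = 30.6). Assumed:

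- 200 trees;
- either one biomarker at d = 0.3 (1% of 100 features, at the upper edge of the effect size in Section 11) or ten at d = 0.5;
- test-retest ICC 0.5 or 0.9, plus one setting with ICC 0.7, ten biomarkers and larger leaves;
- u = 38 for the mixed rows;
- 24 runs per setting.

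Ranges are over the settings run. The last column counts runs with a paired t-test p < 0.05 in the direction of a fall.

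| T0 score, compared with a new T1 measurement | Mean fall | Significant fall |
|---|---|---|
| Training measurement, all patients in training | 0.107 to 0.282 | 100% |
| Training measurement, about half in training | 0.053 to 0.140 | 96 to 100% |
| Experiment 1 measurement, held-out patients only | −0.003 to 0.002 | 0 to 4% |
| Measured anew, all in training | −0.003 to 0.003 | 0 to 12% |
| Measured anew, about half in training | −0.010 to 0.004 | 0 to 4% |
| Out-of-bag at T0, full forest at T1, all in training | −0.132 to −0.038 | 0% |

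With one biomarker at d = 0.3, the setting nearest to Section 11, the fall with about half in training is 0.140 (ICC 0.5) or 0.099 (ICC 0.9). The 12% is 3 of 24 runs and is noise at this precision.

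The last row shows two things. Repairing T0 alone reverses the artefact: the score rises by 0.04 to 0.13. It also suggests that a training patient's newly measured score sits above that patient's out-of-sample score, so levels can be inflated even when the change is not.

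**4. Which T0 does the protocol mean?** Two items favour a new measurement. Section 4 has the algorithm's biomarkers performed at T0 and T1, and which biomarkers those are is known only after months 10 to 12. Section 10 puts the before-and-after evaluation in months 13 to 22. In addition, Sections 2 and 6 require task-based fMRI at T0, while the experiment 1 scans in Section 6 are FLAIR, 3D T1 and resting-state only. Against this, the flowchart has one collection before rehabilitation, shared with experiment 1. Followed literally, it makes T0 the training measurement.

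**The case against.** The strongest reply is that the text, as against the chart, points to a fresh T0, for which the simulated fall is about nil. The flowchart is coarse: it serves three populations and even lists healthy controls in the post-rehabilitation row. This stands, and it is why the bias cannot be called certain. But the chart is the visit schedule that sites will follow, and nothing reconciles it with the text.

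A reader might infer that the score will fall through overfitting whatever is done, and so that aim 3 fails. The documents do not support that. The fall requires the stored measurement to serve as T0. About half of Unit 1's FMD patients would be held out under a balanced split. SFMDRS is not an algorithm output, and the measured biomarkers themselves do not overfit. No section names the mean score as an endpoint or assigns the paired test to it specifically.

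A reader might also infer that aim 2 is contaminated, because Section 11 describes the organic group as "of similar sample size (50 with weakness due to muscle diseases, 50 with ET, and 50 with dystonia, among all Units" and all 150 FMD patients could be set against it. No section states that pooling. Aim 2 concerns specificity, which is computed in organic patients, none of whom trained the model. Sensitivity or AUC would be inflated only if training FMD patients entered the contrast.

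Finally, the learner is not fixed to one random forest: Sections 6 and 12 allow other methods. The size of the artefact is therefore illustrative. Leaving the model version to the analysis plan would be ordinary practice, but the draw and the T0 visit are protocol matters.

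**Conclusion.** The concern holds conditionally. The overlap is nearly certain: about 17 of 34 if Unit 1 supplies half of the training patients, and 11 to 23 on average for shares of 25 to 50. The bias is not certain. If the stored training measurement is used as T0, the mean score falls by 0.05 to 0.14 with about half of the patients in training and no rehabilitation effect. If T0 is measured anew, the artefact is about nil, although training patients' score levels may still be too high.

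The sizes rest on assumed ICC, signal and tree settings, and on equal correlation between all visits. The contrast between the two kinds of T0 held in every setting run. The primary outcome SFMDRS and specificity in organic patients are unaffected. This is an inconsistency to settle before the draw, not a defect that invalidates the sub-study.

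**What to change.** 1. Reconcile Section 4 (Experimental design 3), the Section 7 flowchart and Section 10 on whether T0 is a new measurement taken after the algorithm is built.
2. State that no patient's algorithm score at T0 or T1 comes from a model trained on that patient, and that both time points are scored by the same model in the same way.
3. Name the route. Any of these would do:
   - Score each training patient at both times with the cross-validation model that left that patient out, with any feature selection done inside the fold. With four folds, each model rests on about three quarters of the 150 subjects.
   - Score all 34 with a model fitted without them. Training then keeps about 75 − 17 = 58 FMD patients, so the classes are less balanced.
   - Draw the 34 from held-out Unit 1 patients, if enough exist. A split balanced by Unit gives about 37, which leaves little room for random selection; with 50 Unit 1 patients in training, only 25 remain.
4. Base any FMD sensitivity or AUC reported against the organic group on held-out FMD patients only.

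The cost is protocol wording and one or more extra model fits, with no extra patients. The scoring model in the first two routes differs slightly from the final algorithm, and any aim 2 sensitivity or AUC rests on about 75 FMD patients rather than 150.

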### **Drop-out criteria**

Patients who will not attend all sessions and/or do not perform all clinical and instrumental evaluations will be considered dropouts. A drop-out rate of 10% is estimated.

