**Rehabilitation protocol**

It is a validated 5-day rehabilitation protocol (2 h/day) within a multidisciplinary etiological framework followed by telemedicine program (8,23-25). The in-person 5-days rehabilitation program (2 h/day) will be aimed to re-establish normal movement patterns within a multidisciplinary etiological framework according to a validated rehabilitation protocol for FMD. Treatment will be tailored to the needs of each patient, following general treatment principles: education, exploration of how symptoms affect movement and posture; retraining movements using strategies based on redirection of attention; and development of a self-management plan. Details on the intervention have been described previously (8,23-25). On completion of the 5-days in-person rehabilitation program, the patients will undergo the telemedicine program during one out of the three weekly home-based sessions for 12 consecutive weeks (30 min/session, 1 session/week). It will consist of overground walking at different gait speed, walking backward and sideways, sit-to-stand activities, and squat exercises for lower limb weakness and gait and balance deficits. Bear weight on the hand and straddling a swiss ball will be used for upper limb weakness (31). During each session, the therapist had a video call with the patient via a smartphone or a computer connection according to the patient's availability and preference.

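### The drop-out rule merges a missed session or test with a missing outcome, and the rehabilitation sample size implies that such patients are not analysed even when both SFMDRS scores exist

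*Protocol*

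**What the plan says.** Protocol section 4, under Drop-out criteria, sets the rule: "Patients who will not attend all sessions and/or do not perform all clinical and instrumental evaluations will be considered dropouts". It adds: "A drop-out rate of 10% is estimated". The heading stands after all three experimental designs and is not tied to one of them.

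Section 11 uses the same rate for the rehabilitation sub-study: "for the rehabilitative study Unit 1 will enroll 34 patients", with alpha 0.05, power 90% and a "T0-T1 rehabilitation effect size of 0.605 (mean difference 5.52; Standard deviation 9.11") "on the primary outcome (SFMDRS) and a drop-out rate of 10%(8"). The development set (75 FMD, 75 controls) and the external validation set (75 FMD, 75 controls) of experiment 1 carry no such allowance. Sections 2 and 4 recruit exactly 150 FMD patients and 150 controls.

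The rehabilitation protocol in section 6 has five in-person days, then a telemedicine session that replaces one of three weekly home sessions "for 12 consecutive weeks (30 min/session, 1 session/week").

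Section 12 plans for the sub-study: "Parametric (paired t-test) or non-parametric tests (Wilcoxon test) will be applied accordingly to compare the means for the two-time points (T0, T1"). It also applies Gaussian Process Panel Modeling to all its longitudinal data. For the diagnostic algorithm, models are to be chosen "accounting for type (multi- modal), numerosity, completeness (missing data").

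**The concern.** Two different events share one label. Missing a session is non-adherence and leaves the SFMDRS intact. A missing T1 SFMDRS is a missing outcome and does remove the patient from a paired comparison. Only the second has to cost sample size. Under the section 4 rule, a patient with both SFMDRS scores is a drop-out for missing one 30-minute video call or one instrumental test.

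If drop-outs are left out, two things follow for the rehabilitation sub-study. First, patients are selected on attendance, which happens after baseline and may be related to response. The sub-study has no comparator in which that selection would show. Section 7 intends to use the results to size future trials, so any distortion would carry forward. Second, power is lost for a reason unrelated to missing outcomes.

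In experiment 1, where recruitment equals the stated need, any exclusion puts the development and validation sets below the sizes in section 11.

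**Working it through.** **1. Reproducing the 34.** Inputs from section 11: mean difference 5.52, SD 9.11, so d = 5.52/9.11 = 0.606 (stated as 0.605); alpha 0.05, taken as two-sided because the sidedness is not stated; power 90%. Paired t-test power comes from the noncentral t distribution with n − 1 degrees of freedom and noncentrality 0.605 × √n.

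- n = 30: power 89.3%
- n = 31: power 90.3%, so 31 completers are needed
- Inflation: 31/0.9 = 34.4, stated as 34
- All 34 analysed: power 92.8%

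The inflation makes sense only if drop-outs do not contribute to the SFMDRS comparison. The margin is 34 − 31 = 3 patients.

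**2. What the rule asks of attendance.** Supervised sessions: 5 + 12 = 17. Let q be the chance of attending any one session. With independent absences, the share attending all sessions is q^17. Setting q^17 = 0.90 gives q = 0.9^(1/17) = 0.994, before any missed T0 or T1 evaluation. If all 36 home sessions count, the total is 41 and q = 0.9^(1/41) = 0.997.

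The protocol gives no attendance rate, so q below is an assumption shown as a range.

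| Assumed q | q^17 | Drop-out | Completers of 34 | Power |
|---|---|---|---|---|
| 99.5% | 0.918 | 8% | 31 | 90% |
| 99% | 0.843 | 16% | 29 | 88% |
| 98% | 0.709 | 29% | 24 | 81% |
| 97% | 0.596 | 40% | 20 | 73% |
| 95% | 0.418 | 58% | 14 | 55% |

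**3. If absences cluster within patients.** A beta-binomial model with within-patient correlation ρ (also assumed) gives the share attending all 17 as the product, for j = 0 to 16, of (a + j)/(a + b + j), where a = q(1/ρ − 1) and b = (1 − q)(1/ρ − 1).

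- q = 98%, ρ = 0.3: drop-out about 10%
- q = 97%, ρ = 0.1 or 0.3: drop-out 26% or 15%
- q = 95%, ρ = 0.1 or 0.3: drop-out 39% or 24%, about 21 or 26 completers, power 75% or 84%

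Clustering softens the loss considerably. The 10% then holds at 98% attendance with strong clustering, but not at 95-97% for these values of ρ.

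**4. Experiment 1.** Only protocol figures are needed here. If the rule and its 10% apply and drop-outs are excluded, 150 × 0.9 = 135 FMD patients remain, or 135/2 = 67.5 per set against the stated 75. Keeping 75 after 10% loss would need 75/0.9 = 83.3, so 84 per set. The rule names patients only. Whether controls can be drop-outs is not stated, so no loss is computed for them.

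**5. Sections 4 and 12 side by side.** Section 12 wants models that cope with incomplete data. If every patient with an incomplete battery were removed under section 4, little would be left among patients for those models to cope with. The two are compatible only if such patients stay in.

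**The case against.** The strongest objection is that the protocol never says drop-outs leave the analysis and names no analysis set. Section 12 places no attendance condition on the paired test, and Gaussian Process Panel Modeling is meant for all the longitudinal data. Analysis sets are often left to a statistical analysis plan, which is not at hand. This stands as far as it goes: exclusion is implied by the inflation in section 11 and not declared. But the drop-out rule and the sample size built on it are both in the protocol, so the point concerns stated text and not a missing detail.

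A reader might infer that 10% cannot possibly cover this rule. The documents do not support that. They give no attendance or test-completion rate; 10% is met at about 99.4% independent attendance, or at lower attendance with strong clustering. Section 11 takes its rehabilitation inputs from a previous study, and whether that study counted drop-outs in the same way cannot be checked.

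A reader might also count nine tests at T0 and T1. The nine biomarker tests in section 6 form the battery of experiment 1. Section 4 gives experiment 3 the clinical scales, the biomarkers kept in the algorithm and a task fMRI, so the number of instrumental tests there is not yet known.

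The reach of the rule to experiment 1 is open. Sessions exist only in the rehabilitation programme, and the 10% is applied only to the 34. On the other side, the rule follows all three designs, mentions instrumental evaluations, and the section 7 flowchart tracks drop-out from T0.

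Finally, upward bias is plausible if patients who do well attend more, but nothing in the documents shows it. Patients who improve early may also stop attending.

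**Conclusion.** The point holds in a conditional form. The protocol defines drop-out so that non-adherence and missing outcome are the same thing, and its sample size of 34 implies that such patients are lost to the SFMDRS comparison. If they are excluded, the result is a full-attendance estimate with selection bias of uncertain direction, and 90% power tolerates about three losses. The power range of 55% to 90% rests on assumed attendance of 95% to 99.5% with independent absences, and clustering would raise its lower end. It would be too strong to say that the rehabilitation analysis is already restricted to perfect attenders, because the text does not say so.

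For experiment 1, the fall from 150 to 135 FMD patients uses the protocol's own 10%, but depends on the rule applying there and on exclusion. Section 12 points the other way, so the sections need to be reconciled. The change should be made: the defect is in a stated rule and does not depend on any attendance figure.

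**What to change.** In sections 4 and 11, define drop-out for the primary rehabilitation analysis as a missing T1 SFMDRS. Analyse every patient with T0 and T1 SFMDRS whatever their attendance, and seek the T1 assessment from patients who miss or stop sessions. Report full attenders only as a sensitivity subset, and record attendance separately as adherence.

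For experiment 1, keep subjects with incomplete batteries and handle missing features within the training folds, in line with section 12. State whether the rule covers controls, and restate the evaluable sizes expected for the development and validation sets.

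The cost is a few sentences in two sections and no extra patients. The downside is that the estimated effect may be somewhat smaller once partial attenders are included.
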